### Statistical analyses

Baseline data will be summarized as the number of observations, means, standard deviations, medians, minimums and maximums where the data are continuous and as number of observations and frequencies where the data are categorical. The data will be presented separately by treatment group.

The primary endpoint (mean change in daily step counts from baseline to 12 months) will be analyzed using a constrained linear mixed model approach [61], where the outcome in the model is the mean number of steps per day at each time point, but the baseline mean responses for the treatment groups are assumed equal. This approach has been shown to be robust when missing data depend on baseline values [62]. Predictor variables in the model will include fixed effects for group (usual care as reference and group 1: face-to-face, group 2: telephone), time (baseline as reference, 3 months and 12 months) and the interaction between group and time. A subject level random intercept will be included in the model to allow for correlations arising from repeated measures. There may be some variation to this model after checking its underlying assumptions of multivariate normality, linearity and equal variance and clustering. The primary comparison will be between the combined intervention groups (group 1: face-to-face and group 2: telephone) and usual care. A secondary analysis will examine the difference in step counts at 3 months, and if significant differences are found in the primary analysis, will also explore if there are differences between treatment groups (face-to-face and telephone). Sub group analyses will be conducted by sex, BMI category and diagnosed chronic disease versus none. Sensitivity analyses will explore the impact of individual EP, GP clinic, and after removing the steps imputed from self-reported physical activity. The analysis will be conducted on an intention-to-treat basis with alternative methods of accounting for missing data: multiple imputation, and pattern mixture modelling [63].

Process evaluation will be assessed by calculating adherence with intervention (mean number of sessions completed, average time of intervention delivery for face-to-face and telephone counseling sessions). Intervention fidelity will be assessed by coding of EP checklists.

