### Randomization and blinding

Random allocation of eligible participants was conducted in two stages, and in order to offer participants a service that was geographically accessible they were asked to indicate the suburbs where they would prefer to see an EP. First, eligible patients were randomly assigned in a 1:2 ratio to the usual care group or to the intervention group using a randomized block design stratified by participant gender with block sizes of 6. Second, those allocated to the intervention group were randomly assigned in a 1:1 ratio to face-to-face only or face-to-face and telephone counseling using a randomized block design stratified by participant gender and the suburb location of the EP, using block sizes of 6. The randomization process occurred on computer at a centralized location by an independent statistician. Participants were notified of group allocation by letter. Central randomization allowed concealment of allocation from research assistants and GPs until group assignment had occurred. Blinding of participants and EPs was not feasible. Contamination was minimized as the intervention was not delivered at the primary care site and follow-up data collection occurred by mail, with patient-reported survey and pedometer-assessed step counts, so was not influenced by study team members. The data analyst was blinded to group allocation, as surveys were de-identified and did not contain study group information.

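### The primary model is described as constraining baseline means to be equal, but its listed fixed effects estimate a separate baseline mean in each arm

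*Protocol article*

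**What the plan says.** All of this is in the Statistical analyses section of the protocol article, unless noted.

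- The primary endpoint "will be analyzed using a constrained linear mixed model approach [61], where the outcome in the model is the mean number of steps per day". The model uses all three visits, and it is stated that "the baseline mean responses for the treatment groups are assumed equal".
- The predictors are then listed. The group term is given as "fixed effects for group (usual care as reference and group 1: face-to-face, group 2: telephone"). The remaining terms are given as "time (baseline as reference, 3 months and 12 months) and the interaction between group and time".
- On covariance: "A subject level random intercept will be included in the model".
- On the contrast: "The primary comparison will be between the combined intervention groups (group 1: face-to-face and group 2: telephone) and usual care". Under Randomization and blinding, patients were "randomly assigned in a 1:2 ratio to the usual care group or to the intervention group", and the intervention patients were then split 1:1.

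Nothing in the section says that the group coefficients are set to zero or that the group term is left out.

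**The concern.** A constrained longitudinal model treats baseline as one of the outcomes and gives all arms a single baseline mean. It does so by leaving out the group main effect when baseline is the time reference. The article names that model but lists the terms of a different one.

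Two things are at stake. The first is prespecification: an analyst could fit either model and point to the text, and the two give different primary estimates. The second is precision: the listed terms discard the information that randomization makes the baseline means equal in expectation.

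**Working it through.** **1. Which model the listed terms define.** Three groups at three visits give 3 × 3 = 9 cell means. The listed terms give 1 intercept + 2 group + 2 time + 4 interaction = 9 free parameters, so nothing is constrained. Equal baselines require 1 + 2 + 4 = 7. In simulated data the fitted group 1 coefficient equalled the observed baseline difference to within 2 × 10⁻¹⁰.

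**2. What each model estimates.** Let D0 and D12 be the observed differences (combined intervention minus usual care) at baseline and 12 months. With complete data and a random intercept:

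- listed terms: D12 − D0
- constrained: D12 − r·D0

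The estimates differ by (1 − r)·D0. As an illustration, a 200-step chance imbalance at r = 0.5 gives 0.5 × 200 = 100 steps, a tenth of the 1000-step target.

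**3. The plan's own figure.** The Sample size section gives 79 per group for 90% power, with a difference of 1000, SD 2500 and a 5% level. For a 2:1 comparison without any baseline gain, n per group = 1.5 × (z_α + z_β)² × (2500/1000)².

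- Two-sided: 1.5 × (1.960 + 1.282)² × 6.25 gives 99. Power at 79 is 82.7%.
- One-sided: 1.5 × (1.645 + 1.282)² × 6.25 gives 81. Power at 79 is 89.6%, so the stated figure is nearly reproduced.
- Two-sided with n = 79 is also reached if 2500 is the SD of step counts and either r ≈ 0.60 under the listed terms (variance factor 2(1 − r)) or r ≈ 0.445 under the constraint (factor 1 − r²).

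The sample size therefore does not show which model was meant.

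**4. Precision.** Assume 79 complete per arm (158 v 79), compound symmetry, and SD 2500 at every visit.

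- Var(listed) = 2500² × 2(1 − r) × (1/158 + 1/79)
- Var(constrained) = 2500² × (1 − r²) × (1/158 + 1/79)
- Ratio = 2(1 − r)/(1 − r²) = 2/(1 + r)
- Two-sided 5% power = Φ(1000/SE − 1.96)

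| r (assumed) | SE listed | SE constrained | Variance ratio | Power listed | Power constrained |
|---|---|---|---|---|---|
| 0.3 | 407.6 | 328.6 | 1.54 | 68.9% | 86.1% |
| 0.5 | 344.5 | 298.3 | 1.33 | 82.7% | 91.8% |
| 0.7 | 266.8 | 246.0 | 1.18 | 96.3% | 98.2% |
| 0.9 | 154.1 | 150.2 | 1.05 | about 100% | about 100% |

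If 2500 is instead the SD of change, the variance ratios are the same. Power is then 82.7% at every r under the listed terms, and 95.0%, 91.8%, 88.3% and 84.6% under the constraint. Adding 8 patients per arm with baseline only (87 enrolled) lowers the ratios slightly, to 1.49, 1.30 and 1.16 at r = 0.3, 0.5 and 0.7.

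**5. Bias.** In 150 simulated trials at r = 0.5 with a true effect of 1000, the mean estimates were 1019 (listed) and 1030 (constrained), with empirical SEs of 351 and 319. The Monte Carlo errors are about 351/√150 = 29 and 319/√150 = 26, so neither mean indicates bias.

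**6. Unequal variances.** Under Eligibility and screening, patients averaging more than 7000 steps are excluded. This can compress the baseline distribution but not the follow-up distribution. As an illustration with assumed values, take a baseline SD of 1500, a 12-month SD of 2500 and correlation 0.6. The covariance is 0.6 × 1500 × 2500 = 2.25 million, and the best baseline coefficient is 0.6 × 2500/1500 = 1, which is the change score. Per-patient variances, in millions:

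- change score (listed terms): 6.25 − 4.50 + 2.25 = 4.00
- constrained, plain random intercept with working correlation 0.6: 6.25 − 2 × 0.6 × 2.25 + 0.36 × 2.25 = 4.36, about 9% larger
- constrained, variances free by visit: 6.25 × (1 − 0.36) = 4.00

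Here the constraint with a plain random intercept loses precision. With visit-specific variances it does no worse than the change score.

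**The case against.** The best defence is that the intent is plain. The article names the constrained approach, states the equal-baseline assumption and cites a source before any predictor is listed. The list can be read as naming the factors of a model already constrained, and a journal article need not give the exact parametrisation. The section also allows the model to vary after assumption checks. It stands that the list may be loose drafting and that the loss arises only if it is coded literally. It does not stand that nothing needs correcting: the article goes as far as giving reference levels, and under those levels the list contradicts the constraint.

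A reader might infer several stronger points that the document does not support.

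- *That the listed model leaves chance baseline imbalance unadjusted.* It subtracts the whole baseline difference, with coefficient 1 instead of r.
- *That the cited robustness property is lost.* The only property mentioned concerns missingness that depends on baseline. A likelihood-based mixed model with baseline among its outcomes can handle that with or without the constraint.
- *That the trial is underpowered because of this wording.* The article does not give r, the sidedness of the test, or whether 2500 is the SD of counts or of change. On one reading (SD of counts, two-sided, r ≈ 0.60) the listed terms reach 90%. If 2500 is the SD of change, the 82.7% reflects the sample-size assumptions.
- *That imposing the constraint has no downside.* Step 6 of the working shows otherwise for a plain random intercept.

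**Conclusion.** The contradiction is real and sits in the primary analysis: 9 free parameters are listed for a model described as having 7. The consequence is an ambiguous primary estimate, differing by (1 − r) times the chance baseline difference, together with a possible loss of precision. Neither version is biased under randomization.

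If the terms are coded as listed, the variance of the 12-month contrast is 5% to 54% larger over r = 0.9 to 0.3. That range assumes equal variances over time, compound symmetry and complete data, and r itself is an assumption. The power figures depend in addition on the meaning of the SD and on a two-sided test, so they are illustrations and not established harm. If baseline variance is much lower than follow-up variance, the precision advantage of the constraint can disappear or reverse under the stated random-intercept structure. The wording should be corrected; the estimand and the primary comparison do not change.

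**What to change.** State the fixed effects as an intercept (the common baseline mean), time at 3 and 12 months, and group-by-time terms at 3 and 12 months only. Say that there is no group main effect, or equivalently that the baseline group coefficients are set to zero. Define the primary contrast as the average of the two 12-month group-by-time coefficients; equal weights suit the 1:1 split.

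Because the step cap may truncate baseline, let variances differ by visit, for example with an unstructured covariance over the three visits in place of the random intercept. Fix this before the analysis, so that the constraint delivers its precision gain.

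The cost is a sentence or two of model wording and a few covariance parameters: an unstructured matrix has 6 (3 variances and 3 covariances) against 2 for a random intercept. No additional patients, visits or data are needed.

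### Randomization is stratified by gender, but the primary mixed model lists no stratification factor, so its standard error is slightly too large for the design

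*Protocol article*

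**What the plan says.** Under Randomization and blinding, the first stage allocates usual care against intervention "using a randomized block design stratified by participant gender with block sizes of 6". The second stage divides intervention patients 1:1 between face-to-face and telephone counseling, this time "stratified by participant gender and the suburb location of the EP", again in blocks of 6.

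Under Statistical analyses, the primary model is described term by term. "Predictor variables in the model will include fixed effects for group" opens the list, which continues with "time (baseline as reference, 3 months and 12 months) and the interaction between group and time". Then: "A subject level random intercept will be included in the model to allow for correlations arising from repeated measures". Baseline means are constrained to be equal across groups. One sentence leaves room for change: "There may be some variation to this model after checking its underlying assumptions of multivariate normality, linearity and equal variance and clustering".

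Elsewhere in that section, sex is a subgroup factor, and individual EP and GP clinic are subjects of sensitivity analysis. EP suburb is not mentioned. The primary comparison is the two intervention groups combined against usual care. Face-to-face against telephone is secondary and is explored only if the primary result is significant.

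**The concern.** Stratified blocks force the arms to be nearly balanced on gender. The estimated treatment effect therefore varies less over repeated randomizations than it would under simple randomization, to the extent that gender predicts steps. A model without gender does not know this. It keeps the gender component in the residual and reports a standard error suited to a design with no such balancing. The interval is then wider than it need be, and the test rejects slightly less often than its nominal level.

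For the primary comparison, gender is the only factor involved. EP suburb stratified only the second stage, so it matters only for face-to-face versus telephone. Interval width still counts there, because the article frames that aim as equivalence.

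**Working it through.** **Inputs from the article (Sample size):** 79 evaluable per group, difference 1000 steps/day, SD 2500, 5% level, 90% power. The primary comparison is therefore 158 against 79.

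**Assumed, because the article does not give them:** R², the share of 12-month variance left after baseline that gender explains, and 60% women in the simulation.

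**1. The plan's own sample size, for scale.** With 2:1 allocation, n in usual care = (z_α + z_β)² × 2500² × (1 + 1/2) / 1000².
- One-sided 5%: (1.645 + 1.282)² × 6.25 × 1.5 = 80.3, so 81. Power at 79 is 89.6%. This is close to the stated 79 and 90%.
- Two-sided 5%: (1.960 + 1.282)² × 6.25 × 1.5 = 98.5, so 99. Power at 79 is 82.7%.

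The present point does not depend on which was meant. The check shows only that there is little precision to spare if the test is two-sided.

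**2. Excess in the standard error.** Ratio = 1/√(1 − R²).
- R² = 2%: 1/√0.98 = 1.010
- R² = 5%: 1/√0.95 = 1.026

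The unadjusted SE is 2500 × √(1/79 + 1/158) = 344.5, so the 95% half-width is 1.96 × 344.5 = 675 steps/day. The half-width that the design supports is 675 × √0.98 = 668 at R² = 2%, and 675 × √0.95 = 658 at R² = 5%. The interval is too wide by about 7 to 17 steps/day on each side.

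**3. Effect on the test.** Stratified blocks of 6 were simulated with N = 237, comparing a linear model without gender with one including it, at two-sided 5%. There were 10,000 runs under the null and 6,000 at 1000 steps. The approximation is α = 2 × [1 − Φ(1.96/√(1 − R²))].

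| R² | Approx. α without gender | Simulated α, without / with | Simulated power, without / with |
|---|---|---|---|
| 0% | 5.0% | 5.2% / 5.2% | 81.9% / 82.0% |
| 2% | 4.8% | 4.5% / 4.7% | 82.5% / 83.0% |
| 5% | 4.4% | 4.3% / 4.8% | 83.5% / 84.6% |
| 10% | 3.9% | 4.0% / 5.3% | 83.6% / 86.3% |
| 20% | 2.8% | 2.9% / 5.0% | 85.3% / 90.0% |

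The simulation error on α is about √(0.05 × 0.95/10,000) = 0.2 points, so the 2% row shows little beyond noise. The direction is clear in the lower rows. The simulation has no baseline term, so the 10% and 20% rows illustrate the mechanism and do not estimate its size in the planned model.

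**4. What baseline already absorbs.** Suppose gender shifts every time point equally and explains a share r² of the marginal variance, and the baseline-to-12-month correlation is ρ. The share left after baseline is R² = r²(1 − ρ) / [(1 + ρ)(1 − r²)]. With ρ = 0.5 (assumed):
- r² = 2%: 0.010/1.470 = 0.7%, SE ratio 1.003
- r² = 5%: 0.025/1.425 = 1.8%, SE ratio 1.009
- To leave 2–5% after baseline, r² must be 3R²/(1 + 3R²): 0.06/1.06 = 6% up to 0.15/1.15 = 13%.

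If the gender effect is stable over time, the excess may therefore be under 1%.

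**The case against.** The strongest reply is that this is a condensed article whose analysis plan is not shown. Its wording says what the predictors will include, not that nothing else enters, and it permits variation after model checks. That stands as a caution: the article does not show that the final analysis omits gender. But it is not merely silent on covariates. It sets out the model's terms, and that list does not match the randomization. The permitted variation depends on assumption checks and names no stratification factor. A subgroup analysis by sex examines effect modification and does not adjust the primary contrast. A sensitivity analysis by individual EP is related to EP suburb but is not the second-stage stratum.

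The reply on size also stands. The error is conservative, and at R² of 2–5% the simulated power loss is 0.5 to 1.1 points. Baseline steps probably absorb part of the gender effect, and eligibility excludes people averaging above 7000 steps/day.

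A reader might infer three stronger things that the document does not support:
- That the primary estimate is biased or the primary test invalid. Omitting a balanced factor does neither in this linear model.
- That suburb should have been in the primary comparison. It did not stratify the allocation to usual care.
- That preferred suburb supplies the stratum in every arm. Participants could name several suburbs, whereas the stratum is the EP's location. Nothing shows that the two coincide for usual care.

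**Conclusion.** The mismatch is real and its effect small. As listed, the primary model leaves out gender, the one factor that stratified the primary comparison, and its standard error is slightly too large for the design used. The excess is about 1–2.5% if gender explains 2–5% of the variance left after baseline, equivalent to giving up 2–5% of the sample (about 5 to 12 of 237). With a stable gender effect and a correlation of 0.5, a marginal share of 2–5% leaves an excess of only about 0.3–0.9%. These ranges are assumptions, since the article gives neither gender's share of variance nor the correlation. For face-to-face versus telephone, EP suburb is omitted as well. No size can be put on that, and the contrast is secondary and conditional. The change is worth making because it costs almost nothing, not because a conclusion is likely to turn on it.

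**What to change.** State in the analysis plan, before unblinding, that the primary model includes gender and gender-by-time as fixed effects in addition to the listed terms, with gender as recorded at randomization. The interaction is needed so that the gender effect at 12 months need not equal that at baseline. The constraint of equal baseline means across groups then applies given gender.

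For the secondary face-to-face versus telephone contrast, fit the model among intervention participants and include the stratum actually used at the second stage: gender and EP suburb, with suburb grouped or taken as a random effect if cells are small. Preferred suburb should not stand in for the stratum in usual care.

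The cost is wording and a few degrees of freedom: one for gender and two for gender-by-time over three time points, plus whatever suburb needs in the secondary contrast. The factors were recorded for randomization, so no new data are required.

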## Abstract

**Background:**

Physical inactivity is fourth in the list of risk factors for global mortality. General practitioners are well placed to offer physical activity counseling but insufficient time is a barrier. Although referral to an exercise specialist is an alternative, in Australia, these allied health professionals are only publicly funded to provide face-to-face counseling to patients who have an existing chronic illness. Accordingly, this trial aims to determine the efficacy of GP referral of insufficiently active patients (regardless of their chronic disease status) for physical activity counseling (either face-to-face or predominately via telephone) by exercise specialists, based on patients’ objectively assessed physical activity levels, compared with usual care. If the trial is efficacious, the equivalence and cost-effectiveness of face-to-face counseling versus telephone counseling will be assessed.

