**Discussion:**

If referral of primary care patients to exercise specialists increases physical activity, this process offers the prospect of systematically and sustainably reaching a large proportion of insufficiently active adults. If shown to be efficacious this trial provides evidence to expand public funding beyond those with a chronic disease and for delivery via telephone as well as face-to-face consultations.

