A recent systematic review and meta-analysis of eight randomized controlled trials (5190 participants) assessing the impact of exercise referral schemes concluded that considerable uncertainty remains as to the efficacy of referral schemes for increasing physical activity, fitness or health indicators for people with or without a medical diagnosis, and whether they are an efficient use of resources [17]. The review authors concluded there was significant heterogeneity across the current trials and recommended the conduct of further trials of these schemes, particularly ones that incorporate theory-driven interventions [17]. In addition, since all but one of the included 8 trials relied on a self-report measure of physical activity, trials that use an objective measure of physical activity are required. All eight of the trials in the Pavey review [17] referred inactive patients to a structured, supervised exercise program that was typically 10–12 weeks in duration, and held at leisure centres, clinics, or parks. None of the trials utilized individual coaching by a qualified exercise professional, and the development of an individualized unsupervised exercise plan. Only three trials had follow-ups of 12 months, and none longer than 12 months.

Anokye and colleagues [30] examined the cost-effectiveness of exercise referral schemes and concluded that whilst they are associated with a modest increase in lifetime costs and benefits, the cost-effectiveness is highly sensitive to small changes in the effectiveness and cost of schemes. It is therefore important to evaluate the various models of referral and compare cost-effectiveness for different delivery modes (e.g., face-to-face, telephone).

The NewCOACH pragmatic randomized controlled trial described here has two aims. Firstly to determine the efficacy of GP referral of insufficiently active patients (regardless of their chronic disease status) for physical activity counseling by EPs (either face-to-face or predominately via telephone), based on patients’ objectively assessed physical activity levels, compared with usual care. Secondly to compare the equivalence and cost-effectiveness of face-to-face and telephone counseling.

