### Sample size

A sample size of 79 participants per group will provide 90% power to detect a differential increase of 1000 steps per day at 12 months between the two intervention groups and the usual care group at the 5% significance level. This sample size was calculated assuming that the usual care group will increase their average daily step count by 1000 steps, and the standard deviation of 2500 observed in the pilot study. Attrition rates are estimated to be 10% over the twelve month period [60]. This results in a total required sample of 261 (n = 87 per group).

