## Discussion

The NewCOACH study is a three-arm pragmatic randomized trial that aims to determine the efficacy of GP referral of insufficiently active patients (regardless of their chronic disease status) for physical activity counseling (either face-to-face or predominately via telephone) by exercise specialists, based on patients’ objectively assessed physical activity levels, compared with usual care. If the trial is efficacious, the equivalence and cost-effectiveness of face-to-face counseling versus telephone counseling will be assessed.

Strengths of this study include the pragmatic design, the use of an objective measure of physical activity, the use of qualified exercise specialists (EPs) to deliver the theory-based behavior change counseling, and the 12 month follow-up to assess maintenance of behavior change. Limitations of the study include that only a sub-sample will provide accelerometer data.

If the physical activity counseling is efficacious, this will have implications for the design of future exercise referral schemes and EP funding models both in Australia and internationally. If the trial demonstrates that referral to an EP for coaching is an effective way to get people more active, it will be very attractive to GPs to make greater use of CDM pathways. Current funding legislation in Australia restricts CDM to those with an existing chronic disease [64]. If improvements in physical activity can be demonstrated for previously inactive but otherwise healthy adults in this trial, this will provide support for expansion in the eligibility criteria for the Medicare allied health initiative to include insufficiently active patients who do not have a chronic condition. This would be a significant shift away from just treatment of disease, and would acknowledge the role of allied health professionals in preventing disease in partnership with primary care clinicians. In addition, Medicare funding currently only recognizes face-to-face consultations. Evidence that telephone coaching is equally or more effective could lead to the funding of EP services for telephone delivery which would increase the reach and flexibility of this service.

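### The second aim is equivalence of face-to-face and telephone counseling, but the only step-count analysis stated for that contrast is a search for differences, which cannot establish equivalence

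*Protocol article*

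**What the plan says.** The Background section of the protocol article closes with two aims, of which the second reads "Secondly to compare the equivalence and cost-effectiveness of face-to-face and telephone counseling". The Background part of the Abstract repeats it, conditional on efficacy: "the equivalence and cost-effectiveness of face-to-face counseling versus telephone counseling will be assessed". The Discussion section does the same.

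Under Statistical analyses, "The primary comparison will be between the combined intervention groups (group 1: face-to-face and group 2: telephone) and usual care". The comparison between modes is part of a secondary analysis. It is reached only "if significant differences are found in the primary analysis", and then the trial "will also explore if there are differences between treatment groups (face-to-face and telephone"). Nothing else is said about how step counts in the two modes will be compared.

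The Sample size section is written for intervention against usual care: "A sample size of 79 participants per group will provide 90% power" for a differential increase of 1000 steps per day, with SD 2500.

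The Discussion section says what the mode comparison may be used for: "Evidence that telephone coaching is equally or more effective could lead to the funding of EP services for telephone delivery". The Discussion part of the Abstract likewise links efficacy to public funding "for delivery via telephone as well as face-to-face consultations".

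**The concern.** Equivalence is shown when a confidence interval for the difference lies wholly inside a margin. A test for differences asks whether the interval excludes zero. With a wide interval the second question can be answered no while the data remain compatible with a large loss of benefit. The aim and the stated analysis therefore do not match. No other criterion for the contrast is given, so a null result is the natural thing to quote in support of equal effectiveness.

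The gate does not close the gap. The pooled test concerns the average of the two modes, so a strong face-to-face effect with a weak telephone effect can make it significant. It does not by itself show that telephone counseling works. What is at stake is the funding argument for telephone delivery, not the primary conclusion about referral.

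**Working it through.** **Inputs.** From Sample size: 79 evaluable per group, SD 2500, target effect 1000 steps/day, 5% level (sidedness not stated). From Randomization and blinding: 1:2 usual care to intervention, then 1:1 between modes. The document gives no equivalence margin, so 500, 750 and 1000 are assumptions; 1000 equals the whole effect sought over usual care. Normal approximation throughout.

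**The plan's own figure.** For combined intervention against usual care (158 v 79), SE = 2500 × √(1/79 + 1/158) = 344.5.
- One-sided 5%: power = Φ(1000/344.5 − 1.645) = 89.6%, so the stated 90% reproduces.
- Two-sided 5%: power = 82.7%.

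Either way, the calculation does not address one mode against the other.

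**Precision of telephone v face-to-face (79 v 79).**
- SE = 2500 × √(2/79) = 397.8.
- 90% half-width = 1.645 × 397.8 = 654; 95% half-width = 1.96 × 397.8 = 780.

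**Difference test, two-sided 5%.** P(non-significant | true difference d) = Φ(1.96 − d/397.8) − Φ(−1.96 − d/397.8).
- d = 500 (half the target effect): about 76%.
- d = 750: about 53%.

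**Two one-sided tests at 5% each, true difference zero.** Power = max(0, 2Φ(M/397.8 − 1.645) − 1).
- M = 500: 0%.
- M = 750: 2Φ(0.240) − 1 = 19%.
- M = 1000: 2Φ(0.869) − 1 = 62%.

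Evaluable n per arm for 80% power = 2 × [2500 × (1.645 + 1.282)/M]², which gives 429, 191 and 108 for the three margins, against 79 planned.

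**Sensitivity to precision.** Suppose the effective SD were 2239. This is an assumed value, chosen because it would make 79 per group give 90% two-sided power for the primary contrast: 1000/[(1.96 + 1.282) × √(1/79 + 1/158)]. The half-widths become 586 (90%) and 698 (95%), and power becomes 0%, 35.5% and 75.5% at the three margins.

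**Does the gate help?** With equal arms and common variance, the covariance between (face-to-face + telephone)/2 − usual care and face-to-face − telephone is (Var − Var)/2 = 0. Passing the gate therefore leaves the 76% unchanged. As an illustration, let the true gains over usual care be 1250 (face-to-face) and 750 (telephone), which average 1000. The gate is passed with probability 0.827 (two-sided 5%), and no mode difference is then found with probability 0.758. Both happen in 0.827 × 0.758 = 63% of trials. With true gains of 1500 and 500 the average is again 1000, and the gate is still passed 83% of the time.

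**The case against.** Four points can be made for the plan.

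1. A reader might infer that non-significance will be declared equivalence. The document does not say so. The analysis is described as exploration, and the Discussion's remark about funding is conditional. This stands: the misreading is a risk left open, not a stated rule.

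2. A reader might also infer that telephone is never set against usual care. That is not so. The mixed model has separate terms for each mode, with usual care as reference, and their interactions with time, so the 12-month contrast of each mode with usual care is estimated. They are simply not named as comparisons. This stands, and it makes the repair easy.

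3. The article condenses a fuller plan, and a margin, an interval level and a testing procedure are commonly left to that plan. Testing modes only after overall efficacy is also a recognised hierarchy. Both are fair, so neither the missing margin nor the gate is the point here. What remains is that the article does state an analysis for this contrast, and that analysis does not answer the aim it states.

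4. It would be too strong to say that equivalence can never be shown for margins under about 654 steps. That figure is an expected half-width, not a bound. The realised width depends on the observed SD, on retention, and on the precision gained from the baseline-constrained repeated-measures model. The article does not say whether SD 2500 refers to change or to a single time point. This stands, but the sensitivity run shows that a moderate gain does not change the picture at margins of 500 or 750.

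**Conclusion.** The mismatch between aim and analysis is real and lies within the article. At the planned size, a null result between modes would carry little information about equivalence. A telephone deficit of half the target effect would go undetected about three times in four. Power to show equivalence is about 0%, 19% and 62% at assumed margins of 500, 750 and 1000 steps.

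These figures rest on 79 evaluable per arm, SD 2500, a two-sided 5% difference test and the normal approximation. Better precision from the model would raise the power somewhat.

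This should be fixed, but it concerns a gated secondary comparison. A reader might infer that the trial's main result is undermined. It is not: the primary endpoint, model and pooled comparison are unaffected.

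**What to change.** - In Statistical analyses, replace the exploration of differences with the 12-month telephone minus face-to-face difference in mean daily steps, with its confidence interval, from the primary model.
- Claim equivalence only if the 90% interval lies wholly inside a margin that has been justified and fixed before unblinding. If no acceptable margin is achievable at this precision, remove equivalence from the aim, the Abstract and the Discussion, and call the comparison an estimate.
- Name the telephone v usual care and face-to-face v usual care contrasts as comparisons. Rest any claim about telephone delivery on the first of these together with the between-mode interval, not on the pooled test.

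The cost is changes of wording in the protocol and analysis plan. No new data or model are needed, because all three contrasts come from the model already planned. The claim about telephone delivery may end up weaker.
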